### Biological sample processing

#### Sulfate and magnesium analysis of blood samples

All blood samples are processed at each site to isolate plasma which is then stored at −20°C. Plasma samples are transported to the lead study site where they are batch-analysed. Plasma sulfate concentrations are measured using ion chromatography with suppressed conductivity detection using a Dionex ICS2000, as previously described.^48^ Plasma magnesium concentrations are quantitated as per routine testing using a Vitros 5.1 FS chemistry analyser.

#### Analysis of plasma and urine samples to calculate FEI sulfate

Urine samples are stored at −20°C and batch-analysed. The cotton wool ball is thawed and centrifuged to obtain urine for analysis. Urinary and plasma sulfate concentrations are measured as previously described.^48^ Urinary and plasma creatinine is measured as per routine testing using a Vitros 5.1 FS chemistry analyser. FEI sulfate is calculated using the formula: (urinary sulfate mM×plasma creatinine mM)/(plasma sulfate mM×urinary creatinine mM).

#### Genetic analysis of DNA samples

DNA isolated from blood samples (QIASymphony, QIAGEN) of mother and infant pairs is screened for sequence variants in the *SLC13A4* gene (infant samples) and *SLC13A1* gene (maternal and infant samples) using paired end sequencing on a MiSeq sequencer (Illumina) running 2×150 bp chemistry version 2. Data analysis including alignment to the reference genome hg19 and variant calling is carried out using QIAGEN’s online GeneRead Variant Analysis portal.

### Antenatal and neonatal data

Details regarding dose/duration/timing of the loading dose and maintenance infusion of MgSO_4_, along with maternal weight, are recorded.

Antenatal/maternal and delivery data are also recorded, including antenatal steroid administration, primary reason for preterm birth, whether inborn or outborn from tertiary centre, mode of birth, and date and time of birth.

Neonatal data collected includes expected date of delivery, gestational age and weight at birth, sex, singleton/multiple, Apgar scores (1 and 5 min). CRIB score^49^ data are collected if available. Details of potential factors affecting plasma sulfate concentration are also noted, specifically date/time of any blood transfusions administered within the blood sampling period, and date when ferrous sulfate commenced.

### Short-term outcome data

#### IVH and PVL

Worst grade of IVH (0-IV) and worst PVL (including areas involved, laterality and presence of cystic changes) are coded from reports of routine cranial ultrasound scans on days 5 and 28, and at corrected GA 34–36.

#### Retinopathy of prematurity

Worst stage of ROP (0–5), for each eye, including presence of ‘plus’ disease, and any treatment interventions, is coded from routine ophthalmological review.

#### Capillary haemangioma

Number and size of any capillary haemangiomas is recorded prior to discharge, and by caregiver report at 12 weeks CA. This information is supplemented by caregiver report and medical examination at the 2-year assessment.

#### ‘High risk’ of CP at 12–14 weeks CA

Prechtl’s method of qualitative assessment of general movements is used to identify the absence of fidgety movements.^38^ Absent fidgety movements at this age confers a very high risk for CP at 2 years of age, with sensitivity of 97.6% and specificity of 95.7%.^50–52^

### Outcome data at 2 years CA

#### CP diagnosis

CP is defined according to the recommendations of the Surveillance of Cerebral Palsy in Europe network.^53^ Functional severity of movement disability is classified according to the Gross Motor Function Classification System (GMFCS), which describes five levels according to functional abilities in sitting and walking and the need for assistive devices (walkers or wheelchairs), where level 1 indicates minimal functional impairment.^44 45^ The GMFCS descriptors appropriate to the child’s CA are used.

#### Cognitive and general development

#### Bayley Scales of Infant and Toddler Development (Bayley-III and Bayley-4^A&NZ^)

The Bayley Scales is a developmental assessment for young children up to 42 months old, yielding standardised composite scores which have a mean of 100 and an SD of 15 for three domains (cognitive, language and motor).^39 40^ The third edition (Bayley-III)^39^ is norm-referenced against US children and was used in this study until the fourth edition, Australia and New Zealand standardised edition (Bayley-4^A&NZ^)^40^ was available (2020).

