### Primary aims

To determine whether there is a relationship between plasma sulfate and/or magnesium concentration in VP/EP infants at 7 days of age and formal diagnosis of CP at 2 years corrected age (CA), or absent fidgety movements^38^ at 12–14 weeks CA as a surrogate outcome when formal clinical assessment is unavailable, with subgroup analyses for EP and VP infants.To determine whether there is a relationship between plasma sulfate and/or magnesium concentration in VP/EP infants at 7 days of age and any adverse neurodevelopmental outcome at 2 years CA; motor, cognitive and language scores as assessed by Bayley Scales of Infant and Toddler Development (Bayley III/4^A&NZ^),^39 40^ behavioural difficulties as assessed by Strengths and Difficulties Questionnaire (SDQ),^41 42^ and a composite ‘any moderate-severe disability’, with subgroup analyses for EP and VP infants.To determine the optimal threshold of plasma sulfate and/or magnesium concentration identifying participants with risk of each adverse outcome; CP, motor/cognitive/language delay, behavioural difficulties, thereby identifying a potential plasma sulfate/magnesium target concentration for supplementation. Separate analyses will be performed for each adverse outcome, and for the composite ‘any moderate-severe disability’, along with separate analyses for EP and VP infants.

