### Recruitment

Women and their partners (‘parents’) are approached before or after delivery to explain the study, and consent is sought within the first few days after delivery.

Recruitment commenced at MMH in July 2015 and at RBWH in August 2015. To accelerate recruitment, the study was expanded to GCUH in June 2019.

Parents of surviving infants recruited into a pilot study of postnatal sulfate concentrations conducted at the lead study site in 2013–2014 (N=52) were contacted for consent to follow-up and inclusion in this study.

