### Follow-up procedures

When participants are 12–14 weeks CA, parents record two videos of their infant at home via the BabyMoves app^43^ which provides a notification reminder when each video is due and uploads the videos for scoring (figure 1). Videos are scored independently by two expert assessors according to Prechtl’s method of qualitative assessment of general movements, fidgety period.^38^ Each assessor observes both videos of an infant and independently assigns one score; fidgety movements present (FM+)/fidgety movements absent (FM−)/abnormal fidgety movements. In the case of disagreement between the assessors, a third independent assessor reviews the videos. The assessors are not staff members at any of the recruitment centres, and are blinded to any clinical information, other than all infants being VP/EP and their CA when the video was taken. Infants assigned ‘FM−’ are identified as ‘high risk of CP’ and appropriate clinical referrals are made. If there is subsequently no further follow-up information regarding formal diagnosis of CP, these infants are classified as having CP.

Subsequent follow-up is arranged with the child’s main caregiver (biological mother in most cases).

Participants undergo a comprehensive face-to-face neurodevelopmental assessment at 2 years CA (figure 1).

A formal diagnosis of CP (or absence thereof) is established by clinical neurological examination by a paediatrician/neonatologist. If CP is diagnosed, the motor type, distribution and functional level on the Gross Motor Functional Ability Classification System (GMFCS) are recorded.^44 45^

Formal assessment of motor, cognitive and language outcomes is conducted using the Bayley Edition III/4^A&NZ^.^39 40^ Scores are calculated using CA.

Deafness and blindness are ascertained by caregiver report and paediatrician/neonatologist assessment, plus ophthalmology/audiology reports if available.

Social/behavioural outcomes are assessed through caregiver completion of the SDQ.^41 42^

If assessment at 2 years CA has not been attended, caregivers are invited to attend at any point thereafter. If the child is beyond the age range for the Bayley assessment, cognitive assessment is performed using the Wechsler Preschool and Primary Scale of Intelligence (WPPSI-IV^A&NZ^).^46^

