#### Composite outcome of ‘any moderate-severe disability’

This is defined as any of the following:

CP, GMFCS levels 3–5.Moderate to severe global developmental delay—cognitive and language scores on formal developmental assessment (eg, Bayley) more than 2 SD below mean.Moderate to severe intellectual impairment—FSIQ on formal assessment (eg, WPPSI) more than 2 SD below mean.In the absence of formal assessment, report by paediatrician or child development service of moderate/severe disability, or ASQ-3 more than 2 SD below mean in at least four domains.Registered as blind.Deafness requiring hearing aids or cochlear implant.Severe behavioural difficulties (SDQ total difficulties score ‘very high’).

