### Statistical methods

#### Primary aims 1 and 2

Descriptive statistics will be used to present the antenatal, intra partum, post partum, neonatal and follow-up characteristics, including plasma sulfate and magnesium concentration, of the cohort. Bivariate relationships will be explored between these characteristics and CP and adverse motor/cognitive/language/behavioural outcomes. Mixed-effects regression models will examine the association between plasma sulfate and magnesium concentrations at 7 days of age with adverse outcomes; site will be included as a random effect, with characteristics known to be associated with the outcome from literature and clinical experience, as well as demonstrating an association in bivariate analyses, included as fixed effects. The number of factors included will be restricted dependent on the prevalence of the outcome. Both unadjusted and adjusted effect estimates will be presented, along with 95% CIs, and p values for the primary model examining CP. An a priori subgroup analysis for <28 weeks versus ≥28 weeks will be undertaken.

#### Primary aim 3

Receiver operator characteristic (ROC) curves will be constructed, using CP/motor delay/cognitive delay/language delay/behavioural difficulties as individual outcomes, and the sulfate concentration as the predictor. The area under the ROC curve (AUROC) will be calculated and presented, along with the 95% CIs. The sulfate concentration that results in the best combination of sensitivity and specificity will be calculated (Youden’s index) for each outcome.

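### Bayley-III (US norms) and Bayley-4 (Australia/New Zealand norms) scores are pooled as one outcome in primary aims 2 and 3, and test edition, which follows birth date, is not a guaranteed model term

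*Protocol article*

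**What the plan says.** All references are to the protocol article.

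- **Instrument.** The Bayley section under Outcome data at 2 years CA says that Bayley-III "is norm-referenced against US children and was used in this study until the fourth edition, Australia and New Zealand standardised edition", and dates the availability of the fourth edition to 2020. One description of the scale serves both editions: "standardised composite scores which have a mean of 100 and an SD of 15 for three domains (cognitive, language and motor".
- **Outcome.** Follow-up procedures names the two editions in one breath: "Formal assessment of motor, cognitive and language outcomes is conducted using the Bayley Edition III/4". Primary aim 2 takes "motor, cognitive and language scores as assessed by Bayley Scales of Infant and Toddler Development" as outcomes, and the Sample size section describes the cognitive and language measures as continuous standard scores.
- **Cut-off.** One criterion of the composite is "cognitive and language scores on formal developmental assessment (eg, Bayley) more than 2 SD below mean". It makes no distinction by edition.
- **Model.** Under Statistical methods for primary aims 1 and 2, site is a random effect. The fixed effects are "characteristics known to be associated with the outcome from literature and clinical experience, as well as demonstrating an association in bivariate analyses", and their number is limited according to how common the outcome is. Neither edition nor birth year is named.
- **Aim 3.** ROC curves and Youden's index use sulfate as the predictor and motor, cognitive and language delay among the outcomes. No covariates are described.
- **Calendar.** Infants were born in 2013–2020. Two sites began recruiting in July and August 2015, and "the study was expanded to GCUH in June 2019". Infants from a 2013–2014 pilot may also be included.

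**The concern.** Each edition is scaled to 100 and 15 in its own norm population. A child of given ability need not obtain the same score on both, and 2 SD below the mean need not mark the same ability. The article discloses the change of norms and then defines a single outcome across it.

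The edition used depends on the date of testing, and so mostly on date of birth. If an edition difference exists, part of the variation in Bayley scores is an artefact of the calendar. This would shift the proportion classed as delayed between early and late births. If day-7 sulfate also changed over the recruitment years, for example through changing use of antenatal magnesium sulfate, the artefact would leak into the sulfate association. Aim 3 is meant to suggest a target concentration for supplementation, so a case definition that changes partway through the cohort matters there too.

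**Working it through.** The article states no figure on this point, and aim 2 has no sample size calculation to reproduce. Three checks follow.

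**1. Who was tested on which edition?**

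Date at 2 years CA = birth date + 24 months + (40 weeks − gestational age). The last term is 57 days at 31+6 weeks and 112 days at 24+0 weeks. The month of the switch is not given, so I take 1 January to 31 December 2020 as the range and assume assessment on time.

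- Switch on 1 January 2020: Bayley-III only for births before 11 September 2017 (24+0 weeks) to 5 November 2017 (31+6 weeks).
- Switch on 31 December 2020: births before 10 September 2018 to 4 November 2018.
- With even recruitment to December 2020, Bayley-III covers about 39% to 61% of the birth window at the two 2015 sites.
- Pilot infants reach 2 years CA by April 2017 at the latest, all in the Bayley-III era.
- The first infants at the third site (taken as born 1 June 2019) reach it between 28 July and 21 September 2021, so that site should have no Bayley-III.

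Edition is therefore close to a function of birth date within two sites and constant at the third. A site effect can take up part of the third site's difference, but not a change over time within the other two.

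**2. What would an edition difference do to the cut-off?**

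For a single score with SD 15, P(score < 70) = Φ((70 − mean − shift)/15). The cohort mean (90 or 95) and the shift are assumptions, and both directions are shown.

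| Assumed mean | No shift | 5 points higher | 5 points lower |
|---|---|---|---|
| 95 | Φ(−1.67) = 4.8% | Φ(−2.00) = 2.3% | Φ(−1.33) = 9.1% |
| 90 | Φ(−1.33) = 9.1% | Φ(−1.67) = 4.8% | Φ(−1.00) = 15.9% |

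A 3-point upward shift gives 3.1% (mean 95) or 6.3% (mean 90); a 7-point upward shift gives 1.6% or 3.6%.

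**3. What would it do to the sulfate slope?**

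Let π be the Bayley-III share, g the difference in mean day-7 sulfate between the edition eras in SD units, and d the edition shift in points. With edition omitted, bias in the slope (points per SD of sulfate) ≈ d × π(1 − π) × g. With d = 5 and π = 0.5, both assumed:

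- g = 0: 0
- g = 0.2: 5 × 0.25 × 0.2 = 0.25
- g = 0.5: 5 × 0.25 × 0.5 = 0.625

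Moving π to 0.4 or 0.6 hardly matters (0.24 and 0.60 for the last two lines). At g = 0.5, d = 3 gives 0.38 and d = 7 gives 0.88.

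For comparison, the standard error of the slope is about 15/√1324 = 0.41. It would be larger in practice, because children followed up only by telephone or tested on the Wechsler scale have no Bayley score.

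The added noise is small: the score SD rises from 15 to √(225 + 25 × 0.25) = 15.2, about 1.4%.

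**The case against.** The strongest reply is that this is a condensed article, that an analysis plan may deal with edition, and that the covariate rule already could. The last part stands. The bivariate step covers follow-up characteristics, and edition can fairly be read as one. A reader might infer that edition is shut out of the models; the article does not say so. What remains is that entry depends on a data-driven screen and a limit on covariates, whereas a known change of norms can be handled by design. Nor would the screen help the ROC analyses, for which no covariates are described.

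Second, site is in the model as a random effect, which partly deals with the all-Bayley-4 third site. That also stands, and leaves the within-site change at the two 2015 sites.

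Third, a reader might set an assumed 5-point shift beside the slope detectable with 80% power, 2.80 × 0.41 ≈ 1.15 points per SD, and conclude that the artefact is about four times the detectable effect. That compares a difference in means with a slope. By the formula above, a bias of 1.2 points would need g = 1.2/1.25 = 0.96 SD of sulfate drift, and nothing in the article supports drift of that size.

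Fourth, the tail proportions concern one score. The composite criterion, as worded, asks for low cognitive and language scores together, does not use the motor score, and is one of several criteria. The article also states no 2 SD rule for the delay outcomes in the ROC analyses, and describes aim 3 as predominantly exploratory. These limits are accepted.

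**Conclusion.** The point holds in a limited form. The plan as written pools two differently normed scales, edition closely follows birth date at two of the three sites, and adjustment for it is possible but not assured.

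The consequence is conditional. The article gives neither the size nor the direction of an edition difference, and no evidence that sulfate drifted over the years. If the editions agree in this population, nothing is lost. If they differ by an assumed 5 points, the proportion below 70 on a single score roughly halves or nearly doubles, depending on direction, and the scores become slightly noisier. Bias in the sulfate slope needs sulfate drift as well: none without it, and about 0.25 to 0.6 points per SD for assumed drifts of 0.2 to 0.5 SD, which is roughly 0.6 to 1.5 standard errors. The article does not support a claim that the sulfate results will be confounded, only that the plan does not secure them against it.

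Primary aims 2 and 3 are affected. Cerebral palsy, the outcome on which the study is powered, does not use Bayley scores and is untouched.

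**What to change.** Prespecify Bayley edition as a fixed effect in every model of Bayley scores and of Bayley-based delay, whatever the bivariate screen shows. As a sensitivity analysis, report the sulfate estimates, the composite and the ROC results by edition. Because some assessments were delayed by the pandemic, edition is not wholly determined by birth date, which helps in estimating its effect.

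The cost is one degree of freedom, and the edition should be on record with each test. Precision falls a little in the adjusted model if sulfate drifts: at g = 0.5 and π = 0.5, edition explains 0.25 × 0.25 = 0.0625 of the sulfate variance, so the standard error rises by a factor of 1/√0.9375 = 1.03. Within-edition estimates are less precise: with half of 1324 infants in each, the standard error is about 15/√662 = 0.58 instead of 0.41. They should be read as a check on consistency, not as separate tests.

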#### Wechsler Preschool and Primary Scale of Intelligence

The WPPSI-IV^A&NZ^ is a measure of cognitive development for preschoolers and young children between the ages of 2 years 6 months to 7 years 7 months.^46^ It yields a Full-Scale IQ (FSIQ) and several subscales; above the age of 4 years these are: verbal comprehension, visual spatial, fluid reasoning, working memory and processing speed.^46^

#### Ages and Stages Questionnaires

The ASQ-3 is a parent/caregiver-completed developmental screening tool for young children up to 66 months of age.^47^ There are 21 age-specific questionnaires with assessments in five developmental domains: communication, problem-solving, personal-social, gross motor, fine motor skills.^47^ The score for each domain is categorised according to normative data obtained on US children.^47^ Scores below the 1 SD cut-off at 24 months using the ASQ-2 have reasonable sensitivity (83.6%) in identifying neurodevelopmental delay.^54^

#### Other disabilities and difficulties

Deafness is defined as severe auditory deficit requiring hearing aids or cochlear implant.

Blindness is defined as a severe bilateral visual deficit affecting function.

Social/behavioural difficulties are assessed using the SDQ for 2–4 years old, which is a parent/caregiver-completed behavioural screening questionnaire.^41 42^ There are 25 questions giving scores in five domains: emotional symptoms, conduct problems, hyperactivity/inattention, peer relationship problems, prosocial behaviour.^41 42^

#### Composite outcome of ‘any moderate-severe disability’

This is defined as any of the following:

CP, GMFCS levels 3–5.Moderate to severe global developmental delay—cognitive and language scores on formal developmental assessment (eg, Bayley) more than 2 SD below mean.Moderate to severe intellectual impairment—FSIQ on formal assessment (eg, WPPSI) more than 2 SD below mean.In the absence of formal assessment, report by paediatrician or child development service of moderate/severe disability, or ASQ-3 more than 2 SD below mean in at least four domains.Registered as blind.Deafness requiring hearing aids or cochlear implant.Severe behavioural difficulties (SDQ total difficulties score ‘very high’).

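### The disability composite counts blindness only by registration, although the protocol defines and ascertains blindness by function

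*Protocol article*

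**What the plan says.** Three places in the Protocol article bear on blindness.

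- **Other disabilities and difficulties** gives the definition: "Blindness is defined as a severe bilateral visual deficit affecting function".
- **Follow-up procedures** gives the sources: "Deafness and blindness are ascertained by caregiver report and paediatrician/neonatologist assessment, plus ophthalmology/audiology reports if available".
- **Composite outcome** lists the criteria under the rule "This is defined as any of the following". The visual criterion is "Registered as blind", with nothing further.

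Hearing is handled consistently. The definition reads "Deafness is defined as severe auditory deficit requiring hearing aids or cochlear implant", and the composite criterion reads "Deafness requiring hearing aids or cochlear implant".

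The composite also has a fallback based on clinician or service report, but it opens with a condition: "In the absence of formal assessment, report by paediatrician or child development service of moderate/severe disability".

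The composite is an outcome under primary aim 2. Under primary aim 3 the article adds: "Separate analyses will be performed for each adverse outcome, and for the composite ‘any moderate-severe disability".

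**The concern.** One construct has two definitions. The first concerns how well the child sees and functions. The second concerns whether an administrative step has been taken. Registration appears nowhere else in the article: it is not defined, no register is named, and it is not listed among the data collected.

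The two can disagree for the same child. A severe bilateral deficit confirmed by the examining doctor meets the definition, but without registration it does not meet the composite criterion. Whether and when a family registers a child need not follow the severity of the deficit. The age at assessment also varies: families who miss the 2-year visit may attend later, and the pandemic delayed some assessments. If registration accrues with age, the same impairment could be coded differently according to when the child was seen.

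At stake is the correct classification of a small number of children in an outcome that serves two of the three primary aims.

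**Working it through.** The article states no figure for this point, so there is none to reproduce. The check is a comparison of text, followed by a bounded illustration.

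**Step 1. Set definition against composite criterion.**

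| Construct | Definition | Criterion in the composite | Agree? |
|---|---|---|---|
| Blindness | Functional, severe, both eyes | Registration status | No |
| Deafness | Severe, needing a hearing device | Needing a hearing device | Yes, same device test |

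The hearing row shows that the composite can carry a definition over unchanged. Only the visual criterion departs from its own definition.

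**Step 2. Ask whether the functional definition has another use.** The primary and secondary aims name cerebral palsy, the developmental scores, behaviour, the composite, haemorrhage, retinopathy and haemangiomas. None analyses blindness as an outcome in its own right. Blindness enters an analysis only through the composite, and there the functional definition is not applied.

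**Step 3. Trace one child through all seven criteria.** Take a child who has had the Bayley assessment, has a doctor-confirmed severe bilateral visual deficit, and is not registered.

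1. Cerebral palsy at GMFCS levels 3–5: not present.
2. Cognitive and language scores more than 2 SD below the mean: not met.
3. Full-scale IQ more than 2 SD below the mean: not met.
4. Clinician report or ASQ-3: not available, because a formal assessment exists.
5. Registered blindness: not met.
6. Deafness needing a device: not present.
7. Very high SDQ total: not met.

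The child is coded as having no moderate-severe disability, although the article's own definition calls the child blind.

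**Step 4. Illustrate the size under stated assumptions.** The article gives no blindness rate, registration rate or expected composite rate. Suppose 0.5% to 1% of the 1324 children required for analysis are blind by the functional definition, and 30% to 70% of those are unregistered when assessed. All four percentages are assumptions.

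- Blind children: 1324 × 0.005 = 6.6 to 1324 × 0.01 = 13.2
- Missed by the visual criterion: 6.6 × 0.3 = 2.0 to 13.2 × 0.7 = 9.3
- As a share of the cohort: 0.005 × 0.3 = 0.15% to 0.01 × 0.7 = 0.7%

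Under these assumptions, the loss to the whole composite is at most these numbers, since some of the children will qualify through another criterion.

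**Step 5. Ask what the loss does to the estimate.** The criterion misses true cases and adds no false ones. Let *s* be the proportion of true composite events that are captured. If *s* does not vary with sulfate, the observed risk at sulfate level *x* is *s* × P(event | *x*). The factor *s* cancels from any ratio of risks, and the cost is mainly precision. An odds ratio moves slightly, and very little when the lost share is small. Bias of any note needs *s* to vary with sulfate, that is, the missed cases must relate to sulfate differently from the events that are kept.

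**The case against.** The strongest defence is that registration is a deliberate, stricter threshold. The composite narrows other outcomes too: cerebral palsy is graded at every GMFCS level but counts only at levels 3–5, and of the SDQ only a very high total score counts. On that pattern, registration would be an objective cut for severity. This is weakened by two facts: the definition already requires a severe bilateral deficit, and it serves no other analysis. If a stricter threshold was meant, the article does not say so.

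It may also be said that registered is loose wording for recorded, or that a caregiver can be asked about registration and that the form's items belong to the full protocol. Either is possible, and the absence of a form item is not the point here. Both definitions are printed and they differ, so they need aligning on any of these readings.

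The objection on consequence largely stands. Blindness is one of seven criteria, the composite is not the powered outcome, p values are planned for the primary cerebral palsy model, and aim 3 is described as mainly exploratory. A blind child without formal assessment can still enter through a clinician's report.

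A reader might infer that the sulfate association is diluted, because the protocol suggests that retinopathy may stem from sulfate deficiency and retinopathy can impair vision. The documents do not support that as a finding. Dilution would require the missed children to be more strongly related to sulfate than the remaining events, and nothing in the article shows this. Retinopathy is also examined directly under secondary aim 4.

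**Conclusion.** The point holds as a minor but real inconsistency of definition. Taken literally, the composite codes as unaffected a formally assessed child who is blind by the protocol's definition, is unregistered and meets no other criterion.

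The size cannot be derived from the documents and is probably small. The illustrative 2 to 9 children rests entirely on assumed rates. To say that the criterion loses 30% to 70% of its own events would only restate the assumed unregistered share. The expected effect is a few lost composite events and slightly less precision, with bias only if the missed cases relate to sulfate.

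Two stronger readings should be resisted. Not every unregistered blind child is lost, since another criterion may apply. The main result is not compromised either: the cerebral palsy outcome and the sample size of 1324 (1595 with losses) do not depend on this criterion.

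**What to change.** In the Composite outcome section, replace the registration criterion with blindness as defined under Other disabilities and difficulties, ascertained as described under Follow-up procedures. Accept registration as sufficient but not necessary evidence. Keep to the stated ascertainment, which joins caregiver report with a doctor's assessment: where a clinician assessment exists, an unverified caregiver report alone should not be enough, since false positives would be harmful in so rare a category.

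If registration really is the intended threshold, the article should say so and list it among the data collected.

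The cost is one line of wording, settled before the composite is coded. The functional information is already gathered at follow-up, so no new visit or data item is needed. The small downside is somewhat more reliance on clinical judgement than a registry status would involve.
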